#### Randomisation procedures

Clusters will be randomly assigned in a 1:1 ratio to the intervention or control arm following completion of baseline data collection. A restricted randomisation approach will be used to ensure balance across arms with respect to baseline HbA1c levels, key sociodemographic characteristics (such as age, sex, income and education), and cluster size. These parameters will be used to guide the allocation process to maintain equivalence across study arms, thereby strengthening the internal validity of the research. Should any residual imbalances arise post-randomisation, we will adjust for these covariates in the statistical analyses.

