#### Sample size

Based on preliminary data from the diagnostic phase and published literature, the baseline rate of achievement for the composite primary outcome (glycaemic control (HbA1c <8%); blood pressure control (<140/90 mm Hg); and use of statins (statin prescription) -limited to patients ≥40 years-) in the control group is estimated at 30%. The intervention is expected to improve this to ≥50% (absolute effect size of 20%). We have calculated the sample size considering a parallel cluster randomised trial with a cohort design, including baseline and follow-up assessments. The trial is powered at 80% to detect an absolute difference of 20 percentage points between the control group (30%) and the intervention group (50%) on the composite primary outcome, assuming a two-sided significance level of 5%. The design includes six clusters per arm (12 in total) and accounts for the correlation structure of repeated measures using a two-period decay model. Specifically, we assumed an intracluster correlation coefficient (ICC) of 0.05, a cluster autocorrelation of 0.5, and an individual autocorrelation of 0.6. Standard errors were adjusted using a t-distribution to account for the small number of clusters. Based on these parameters, the required sample size before adjusting for attrition is 312 individuals (26 per cluster). Applying an attrition inflation factor of 1.25 (to allow for 20% loss to follow-up), the final sample size increases to 396 individuals (33 per cluster, 198 per arm).

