#### Outcomes

The primary outcome will be a composite outcome including glycaemic control (HbA1c <8%); blood pressure control (<140/90 mm Hg); and use of statins (statin prescription) limited to patients ≥40 years. The source to obtain this data will be routine clinical records.

Secondary outcomes measured through participant questionnaires include user-reported quality of care (key secondary outcome), PHC engagement, system competence, patient confidence in the health system, inequities in outcomes and patient empowerment. User-reported Quality of Care is the overall rating of quality of care from enrolled patients, categorised as ‘excellent or very good’ versus ‘good’ or worse. PHC engagement is measured as the percentage of visits conducted at the PHC level during the data collection period, with positive engagement defined as ≥75% of all non-urgent ambulatory visits.^31^ System competence is defined as ≥75% of enrolled patients per site adhering to the complete set of selected diabetes prevention recommendations from national and provincial guidelines: annual eye exam, yearly foot exam, annual kidney function assessment, annual blood pressure measurement and biannual HbA1c measurement during the follow-up period. Patient confidence in the health system is measured by the combination of three aspects in the e-Cohort survey: health security, endorsement of the current system and trajectory.^32^ Security: We will calculate the percentage of respondents answering ‘somewhat’ or ‘very confident’ to ‘How confident are you that you would receive good quality healthcare if you became very sick?’ and ‘that you could afford the healthcare you needed if you became very sick?’. Confidence: The proportion of respondents indicates that in the past 2 years, the health system has been improving (vs staying the same or getting worse). Endorsement is indicated by agreement that the system works well and needs only minor reforms (vs significant changes needed or need to be completely rebuilt). To assess inequities, we will explore gender, migration status, education and income as potential variables related to underperformance in primary outcomes. Finally, we will measure patient empowerment using the Diabetes Empowerment Scale. This instrument is free and easy to use and has been adapted and validated in its Spanish version.^33^

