#### Data analysis

We will use all available data from all randomised clusters and conduct all analyses on the intention-to-treat (ITT) population, including all clusters and patients in the randomised group, regardless of intervention adherence. Summary statistics will be given for baseline data by treatment group using means, SD, medians, minimum, maximum and quartiles for continuous variables and counts and percentages for categorical variables. We will quantify complete vs incomplete records and describe the characteristics of patients lost to follow-up.

For the composite clinical outcome, the primary ITT analysis will compare the proportion of patients achieving an HbA1c level <8%, blood pressure control <140/90 mm Hg and statin uptake between the trial arms at the end of the study. We expect a good covariate balance between the groups; therefore, the ITT analysis will be performed by comparing proportions. Patient and cluster-level covariates can be included in a mixed-effects logistic regression model to account for the cluster effect and obtain an adjusted estimate of the average treatment effect for within-cluster change.^35^ Adjusted ORs will be reported with 95% CIs, p values and ICCs will be reported to estimate the percentage of variance explained by each level.

For quality of care, we will compare the proportion of patients reporting overall quality of care as ‘excellent’ or ‘very good’ before and after the intervention phase between trial arms using difference-in-difference regression analysis to estimate the average treatment effect. Engagement and confidence in the health system will be evaluated by comparing the proportion of patients achieving the expected threshold in each trial using a χ^2^ test for proportions. Fisher’s exact test will evaluate system competence across participating PHC centres. Direct costs related to diabetes care will be reported for each group. We may expect higher costs in the intervention group due to increased and better utilisation of health services. The mean cost will be analysed considering the variable distribution (non-normal/normal). For all outcomes, we will conduct mixed effects regression adjusted for covariates and clustered by department to provide an average treatment effect for expected change in outcomes within each department.

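### Restricted randomisation balances HbA1c but not the baseline composite, and no adjustment for it is named: lost precision with 12 departments, not bias

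*Protocol article*

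**What the plan says.** Randomisation procedures gives the timing: "Clusters will be randomly assigned in a 1:1 ratio to the intervention or control arm following completion of baseline data collection". The restriction is meant to "ensure balance across arms with respect to baseline HbA1c levels, key sociodemographic characteristics (such as age, sex, income and education), and cluster size". The words *such as* open only the sociodemographic list, so blood pressure, statin prescription and the composite are not covered by it. The fallback reads: "Should any residual imbalances arise post-randomisation, we will adjust for these covariates in the statistical analyses". The covariates meant are most naturally the ones just listed.

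Outcomes defines the endpoint: "The primary outcome will be a composite outcome including glycaemic control (HbA1c <8%); blood pressure control (<140/90 mm Hg); and use of statins", the statin part being limited to patients aged 40 or over. It adds: "The source to obtain this data will be routine clinical records".

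Sample size describes a "parallel cluster randomised trial with a cohort design, including baseline and follow-up assessments".

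Data analysis states: "We expect a good covariate balance between the groups; therefore, the ITT analysis will be performed by comparing proportions". It goes on to say that patient and cluster covariates may enter a mixed-effects logistic model. Later in the same section it commits to covariate-adjusted mixed-effects regression, clustered by department, for every outcome. Neither sentence names the baseline composite.

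**The concern.** The trial randomises 12 departments, six per arm, once. With so few units, the purpose of restriction is to prevent a chance imbalance in whatever predicts the outcome. The cohort design assumes that each department's baseline composite is measured, and allocation waits until baseline collection is complete. The restriction nevertheless uses one of the three components plus sociodemographics and size. Blood pressure control and statin prescription are balanced only so far as they travel with the listed factors.

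The primary comparison of proportions is then justified by an expectation of good balance. That expectation is not secured for the baseline value of the outcome itself. A visible gap in baseline control between arms would make the result harder to interpret, and precision that the sample size appears to rely on would be lost.

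**Working it through.** **Inputs (Sample size section).** Control proportion 30%, intervention 50%; six clusters per arm; ICC 0.05; cluster autocorrelation 0.5; individual autocorrelation 0.6; 26 per cluster before attrition and 33 enrolled.

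**1. The plan's own figures.**
- Attrition: 26 × 1.25 = 32.5, rounded up to 33; 33 × 12 = 396, as stated.
- Correlation between a cluster's baseline and endline proportions: r = [m·ICC·CAC + (1 − ICC)·IAC] / [1 + (m − 1)·ICC]. At m = 26: (0.65 + 0.57)/2.25 = 0.542. At m = 33: (0.825 + 0.57)/2.60 = 0.537.
- Endline-only SE at m = 26: √[(0.21 + 0.25) × 2.25/156] = 0.0815.
- SE adjusted for baseline: 0.0815 × √(1 − 0.542²) = 0.0684.
- Power for 20 points with baseline adjustment: 79.8% with 22 df, which reproduces the stated 80%. The df are my assumption, as the article gives none; 10 df gives 75.0% and a normal reference 83.2%.
- Power of an endline-only comparison: 60% (10 df) to 69% (normal).

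The stated power is therefore matched by an analysis that uses the baseline composite, and not by an endline comparison alone.

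**2. Baseline imbalance with no restriction.** Baseline enrolment is 33 per cluster, so m = 33 applies.
- SD of the arm difference = √[(2/6) × 0.30 × 0.70 × 2.60/33] = 0.074, or 7.4 points (95% range about ±14.6).
- P(|difference| > 10 points) = 18%.

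**3. Imbalance under the listed factors.** The cluster-level correlation between HbA1c and the composite is not given, so I take 0.3, 0.5 and 0.7.
- If HbA1c were perfectly balanced, the SD would be 7.4 × √(1 − c²) = 7.1, 6.4 or 5.3 points.
- A simulation over all C(12,6) = 924 allocations balanced HbA1c and five other factors, the five taken as independent of the composite, and kept the best 10% (92 allocations; the cut is an assumption):

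| Assumed correlation | Listed factors only | Composite added |
|---|---|---|
| 0.3 | 7.1 points | 4.2 points |
| 0.5 | 6.8 points | 4.1 points |
| 0.7 | 6.0 points | 3.9 points |

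By a normal approximation, the listed factors leave about 16%, 14% and 10% of allocations beyond 10 points.

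**4. What reaches the endline.** With equal variances at the two times, the regression slope is r = 0.537. A 10-point baseline gap predicts about 5.4 points at endline, against the 20-point target. In SD terms, 0.537 × (7.1, 6.8, 6.0) = 3.8, 3.6 and 3.2 points under the listed factors, and 0.537 × (4.2, 4.1, 3.9) = 2.3, 2.2 and 2.1 points with the composite added. This variation is a component of the ordinary endline SE (8.1 points at 26 per cluster), not an addition to it.

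**The case against.** The strongest reply is that nothing here is an error. Restricting on one component plus sociodemographics and size is a valid design, and a condensed article may leave final restriction details to a fuller document. That stands as far as validity goes. But the article does fix a list, and the list omits the outcome's own baseline.

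A reader might infer that chance imbalance biases the comparison. The documents do not support this: over the randomisation the estimate is unbiased, and the carry-over is already part of sampling error.

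A reader might also infer that the trial will report only an unadjusted comparison. That is not supported either, because Data analysis commits to covariate-adjusted mixed-effects regression for all outcomes, aimed at change within department, which may well use baseline. What remains is that the primary comparison is described as one of proportions resting on balance, and no adjustment set names the baseline composite.

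Two further inferences go beyond the text. No figure shows that the baseline composite predicts the outcome better than HbA1c does, only that it is prognostic. Nothing shows that statin prescribing clusters by department.

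Availability before allocation is also inferred. Data collection names visits and laboratory tests among the record extracts, not blood pressure or prescriptions, although the cohort sample size presupposes a baseline composite.

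Finally, 924 allocations limit how many factors can be balanced. Dropping sociodemographic ones has a cost, since subgroup and inequality analyses by gender, income and education are planned.

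**Conclusion.** The point holds as a weakness of design and prespecification, not as a bias or a contradiction. The baseline composite is materially prognostic on the article's own correlations (r about 0.54), yet it is named neither as a balancing factor nor as an adjustment variable.

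The 7.4-point SD and the 18% describe allocation with no restriction, which is not the plan. Under the planned factors the SD is about 6 to 7 points, against about 4 if the composite is added. That comparison rests on the assumed HbA1c-composite correlations, on keeping the best 10% of allocations, and on independence of the other five factors.

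Most of the lost precision can be recovered by adjustment alone. The calculations do not measure what restriction would add once that adjustment is made; its further benefit is mainly a more credible single allocation.

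**What to change.** 1. In the primary analysis, prespecify adjustment for the baseline composite, whether or not imbalance appears. This can be done even if departments have already been allocated. It costs one model term and brings the analysis into line with the power calculation.
2. If allocation has not yet occurred, add the department-level baseline proportion meeting the composite to the restriction criteria. Baseline blood pressure control and statin prescription alongside HbA1c would serve as an alternative. Check that enough of the 924 allocations remain acceptable. If too few do, loosen a tolerance or drop a weaker sociodemographic factor, bearing in mind the planned inequality analyses.
3. State in Data collection that blood pressure and statin prescription are extracted at baseline, before allocation.

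If the baseline composite is captured as the cohort design assumes, no new data are needed and the sample size does not change. The downside is slightly fewer acceptable allocations.

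### The protocol is inconsistent on adjusting for the restricted-randomisation variables, and treats balance by design as a reason to leave them out of the primary comparison

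*Protocol article*

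**What the plan says.** Three statements in the Protocol article bear on this.

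- **Randomisation procedures.** "A restricted randomisation approach will be used to ensure balance across arms with respect to baseline HbA1c levels", and also on sociodemographic characteristics (age, sex, income and education are given as examples) and cluster size. The section ends: "Should any residual imbalances arise post-randomisation, we will adjust for these covariates in the statistical analyses".
- **Data analysis, primary outcome.** Good covariate balance is expected, and on that ground the intention-to-treat analysis will compare proportions. No covariate and no cluster term is stated for that comparison. The next sentence makes adjustment optional: "Patient and cluster-level covariates can be included in a mixed-effects logistic regression model".
- **Data analysis, end of the paragraph on secondary outcomes.** For every outcome, a mixed-effects regression with covariate adjustment and clustering by department will be run. The covariates are not named or tied to the restriction variables, and the model is not called primary.

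So adjustment is conditional in one place, optional in another and unconditional in a third.

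**The concern.** Restricting the allocation to well-balanced splits reduces the true variance of the treatment effect, because the balanced variables can no longer differ much between arms. An unadjusted standard error does not know this: it still counts the variation between clusters that those variables explain. The standard error is then too large for the design, the test rejects too rarely under the null, and the precision gained by restricting is not recovered. Reasoning from expected balance to no adjustment therefore runs the wrong way.

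A rule triggered by observed imbalance has a second fault. The composition of the model depends on the allocation that happens to be drawn and on an unstated judgement of what counts as imbalance. With 12 clusters, that choice can move the estimate and the p value.

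The stated power is also involved, because it takes credit for baseline information that the primary comparison, as written, does not use.

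**Working it through.** **Inputs from the Sample size section.** Rates of 30% and 50%, two-sided 5% level, six clusters per arm, 26 patients per cluster before attrition, and this correlation structure: "we assumed an intracluster correlation coefficient (ICC) of 0.05, a cluster autocorrelation of 0.5, and an individual autocorrelation of 0.6".

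**Step 1: reproduce the plan's figure.**

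- Single-period design effect: 1 + 25 × 0.05 = 2.25.
- Correlation of a cluster's baseline and follow-up means: r = (26 × 0.05 × 0.5 + 0.95 × 0.6) / 2.25 = 1.22 / 2.25 = 0.542.
- Design effect with baseline credited: 2.25 × (1 − 0.542²) = 1.588.
- SE = √[(0.21 + 0.25)/156 × 1.588] = 0.0684, so 0.20/SE = 2.92.
- Power is 0.794 to 0.798 with 20 to 22 df, 0.832 with a normal quantile and 0.750 with 10 df. The first range agrees with the stated 80%.
- Attrition: 26/0.8 = 32.5, rounded to 33, and 33 × 12 = 396.

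Without the baseline credit the design effect stays at 2.25. Power at 26 per cluster is then 0.60 (10 df), 0.65 (22 df) or 0.69 (normal).

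**Step 2: simulate the adjustment rule.** Twelve clusters of 26, ICC 0.05, and all C(12,6) = 924 allocations enumerated. Two inputs are assumptions, because the article gives neither: the best-balanced 10% of allocations are kept, and the balancing variables explain a share R² of the between-cluster variance. Each cell has 6,000 runs, so the Monte Carlo error at 5% is √(0.05 × 0.95/6000) = 0.3 points. *Sparse* means two covariates or one summary score.

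| R² | Type I, unadjusted cluster t test | Type I, adjusted | Power, unadjusted | Power, sparse | Power, six cluster-level terms | Type I, two-proportion test ignoring clusters |
|---|---|---|---|---|---|---|
| 0 | 4.6–5.3% | about 5% | 58% | 55% | 36% | 19% |
| 0.3 | 3.5% | about 5% | 58–59% | 64% | 40% | 15–16% |
| 0.6 | 2.1–2.8% | about 5% | 57–58% | 72–73% | 48% | 11–13% |
| 0.9 | 0.8–1.7% | about 5% | 58% | 85–86% | 59% | 6–10% |

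With no restriction, the unadjusted cluster t test stays at 4.6 to 5.3% whatever the R², so the conservatism comes from restricting and then not adjusting.

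Six separate cluster-level terms leave 12 − 2 − 6 = 4 df, with a critical t of 2.776 against 2.228 at 10 df. That is why this column falls below the unadjusted test except at R² = 0.9.

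**Step 3: which rows are plausible?** Between-cluster variance is 0.05/(0.05 + 0.95/26) = 58% of the variance of a cluster mean. The rows R² = 0.3 and 0.6 are therefore about 17% and 35% of cluster-mean variance. The plan's parameters give two anchors, both for the baseline composite:

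- the cluster autocorrelation squared, 0.5² = 0.25 of between-cluster variance, or about 14% of cluster-mean variance;
- the cluster-mean correlation squared, 0.542² = 29% of cluster-mean variance.

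A run at the second anchor gives type I error of 2.1 to 2.3% unadjusted against 4.6 to 5.4% adjusted, and power of 61% against 72 to 74%. The first anchor lies near the 0.3 row, with a gain of 5 to 6 points. Rows 0.3 and 0.6 are thus a reasonable working range: type I error about 2 to 3.5%, power loss about 5 to 15 points.

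**The case against.** **Adjustment is promised.** A reader of the Randomisation section might infer that covariates enter only when imbalance is seen. The document does not support that, because the Data analysis section commits to adjusted mixed regression for all outcomes. This stands. The fault is an inconsistency and an undesignated primary model, not an absence of adjustment.

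**The primary test need not be conservative.** A reader might also infer that the trial's test is too conservative as it stands. That needs three things together: a test that respects clustering, balancing variables that are prognostic at cluster level, and tight restriction. The article states none of them for the primary comparison. Read literally, a comparison of proportions with no cluster term errs in the other direction (6 to 19% type I error above), and restriction only partly offsets this. The Sample size section allows for the ICC and uses a t-distribution, so a clustered analysis is probably intended, but the text does not say so.

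**The size rests on assumptions.** The 10% cut and R² are not in the document. The composite behind both anchors is not a restriction variable, and HbA1c is only one of its three components. The effect may lie at the lower end of the range.

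**The list belongs in the SAP, and timing limits the harm.** The exact covariate list is ordinary SAP content, and its absence is not criticised here. Allocation follows completed baseline collection, so imbalance could be judged before any follow-up outcome exists. Both points soften the concern about data-driven choice. Neither removes the stated rule or the stated reason for an unadjusted primary comparison, which are choices the article makes.

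**Conclusion.** The point holds in a limited form. The Randomisation procedures and Data analysis sections give conditional, optional and unconditional adjustment without saying which is primary, and the reason given for an unadjusted primary comparison is backwards for a restricted design.

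For a cluster-respecting test with prognostic balancing variables and restriction to the best 10% of allocations, leaving them out gives type I error of about 2 to 3.5% and costs about 5 to 15 points of power against a sparse adjusted model. If the variables carry no prognostic information, adjustment costs about 3 points. The direction is firm under those conditions, but the size depends on the assumed R² and cut.

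No change in sample size follows. The claim "The trial is powered at 80% to detect an absolute difference of 20 percentage points" is reproduced, but only with the baseline measurement credited, which is a further reason for the primary model to contain it.

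**What to change.** Reconcile the two sections along these lines:

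- The primary analysis is a model that accounts for clustering by department, with a small-sample correction.
- It always adjusts, whatever the observed balance, for a short set fixed in advance: baseline composite status, baseline HbA1c, age and sex at patient level.
- The remaining restriction variables are entered sparingly or combined into one prognostic score. This includes cluster size, which can only be a cluster-level term.
- A permutation test over the restricted set of allocations is an acceptable alternative, since it respects both the clustering and the restriction.
- Models with covariates added because of observed imbalance are sensitivity analyses only.

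The cost is about one sentence in each section and no new data, since the restriction variables are needed before allocation and the sample size already assumes a baseline assessment. The one downside is that the set must stay sparse: six separate cluster-level terms would leave 4 df and in most scenarios lose more power than they gain.
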